#### Participants recruitment

2.2.2

Youths aged 15–35 will be identified from schools (in-school youths) and communities (out-of-school youths) in the selected states mentioned above. The selection of target states was based on purposive selection, considering their commonality in the IVFs of interest. The second stage will involve the selection of participants from each of the six selected communities (one from a rural and another from an urban local government area (LGA) in each of the selected states). LGA is an administrative division within a Nigeria that functions as the third tier of government, below the national and state levels. The target rural and urban LGA will be randomly selected from each state’s list of LGAs.

The selection of target schools will be facilitated in collaboration with the leadership of the State Ministry of Education, based on pre-selected criteria that can support onsite gardening activities. These criteria include having: a piece of land suitable for farming, access to water, and either a fenced perimeter or good security measures in place. After the school is identified, the researcher will collaborate with school administrators and teachers in the selected communities to recruit eligible in-school and out-of-school youths. Out-of-school youths will be selected from the communities where the selected schools are situated to bridge the gap between the schools and the wider community, ensuring that the gardening projects are inclusive, sustainable, and community-driven. The summary of eligibility criteria for youth selection for the gardening intervention is highlighted as follows:

Be an in-school or out-school youth between 15 and 35 years.Located in the selected LGAs.Should remain enrolled in the selected school for another year while residing in the communities chosen as study sites for the in-school youth.Should reside in communities selected as study sites for another year for the out-of-school youths.

The exclusion criteria include:

Not an in or out-of-school youth located in the selected LGAs.Not within the age bracket (15–35 years).Does not have the willingness to participate in the study.

Youths that would be enrolled in the nutritional education arm of the intervention should:

Own or has a parent who owns an internet-enabled phone that can install the WhatsApp application.Have internet and social media literacy

The exclusion criteria for the nutrition education arm of the intervention are:

Does not own or have good access to the parent’s web-based phone that supports the installation of the WhatsApp applicationDoes not have internet and social media literacyNot willing to participate in the intervention program

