**Methods and analysis:**

This is a non-randomized, mixed-methods study involving youths between 15 and 35 years who will participate in gardening activities and/or interactive nutrition education via WhatsApp. Participants will be provided technical support on growing IVFs, while nutrition education messaging via WhatsApp will include texts, images, and videos on nutrition and healthy eating behavior. Data at baseline will be collected on the study’s primary outcomes (awareness and interest in IVFs, household food security, nutritional knowledge and practices, fruits and vegetables intake, food safety self-efficacy, dietary diversity, anthropometric, and biomarker indicators). In contrast, data collection during the intervention and at post-intervention will include the study’s secondary outcomes (WhatsApp engagement, knowledge retention, and intervention acceptability). Mixed model regression and the Mann–Whitney U Test will be used to analyze the data collected. All analyses will be performed using IBM SPSS (version 23), and the statistical significance will be set at a *p*-value <0.05.

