##### Anthropometric measurement and biomarker Indicator

2.4.1.7

Study participants will be assessed on their height (m) and weight (kg) to determine their Body Mass Index (BMI). WHO Anthro software will be used to assess the anthropometric measurement of participants between (15–18 years old) using the BMI for Age metric; the anthropometric measurement of participants between the age of 19 and 35 will be based on WHO standard of underweight if BMI is <18.5 kg/m^2^, normal or healthy weight if BMI is 18.5 kg/m^2^–24.9 kg/m^2^, overweight if BMI is 25–29.9 kg/m^2^, and obese if BMI ≥ 30.0 kg/m^2^ (52). The participants’ skin carotenoid levels will be assessed using the Veggie Meter to assess their fruits and vegetables intake (53).

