### Data analysis

2.5

Descriptive statistics such as frequency and percentages will be used for the socio-demographic characteristics (such as age, gender, student status, and household size) and other outcome of measures (such as knowledge retention, intervention acceptability, and nutrition-related outcomes) that are categorical variables, while mean and standard deviation will be used for the continuous variables. To assess the possibility of bias resulting from missing data, we will conduct sensitivity analyses by carrying out complete case analyses. As opined by Braun and Clarke, this will ensure the robustness and credibility of our result (61). Mixed model analyses will be used to assess the intervention’s impact on skin carotenoid levels, anthropometrics, and diet diversity score (62, 63). The mixed model analysis was chosen because it accounts for repeated measures and can effectively address issues related to missing data. In these analyses, the intervention arms will be treated as the fixed effect so that the measure’s outcome change between the school gardening-only participants and school gardening and nutrition education participants can be assessed by the coefficients or estimated using the least square means. Time and intervention arm will be included as both main effects and interaction effects. The random effect will account for variability variations between groups that might affect the response. We will control for participant’s age, gender, household size, youth status (out-of-school vs. in-school status), community, and state, by including them as covariates in the adjusted models of the mixed model analysis. Mann–Whitney U Test will be used to compare the acceptability of the nutrition intervention between the groups. The analysis will be performed using IBM SPSS (version 23), and the statistical significance will be set at *p*-value <0.05.

As described by Braun and Clarke (61), the participants’ audio (sessions responses) and video recordings (tasks) from WhatsApp engagement will be analyzed using thematic analysis. We will use inductive coding to deduce the theme directly from the data. The convergent mixed method will be used to integrate the qualitative analysis with the quantitative results. This ensures a proper understanding of how participants experienced and engaged with the intervention.

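### BMI is a primary outcome in women and men aged 15–35, but sections 2.4.1.7 and 2.5 state no handling of BMI values affected by pregnancy or recent delivery

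*Protocol article*

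**What the plan says.** - **Who enrols.** Section 2.2.2 of the protocol article gives the age and status criterion as "Be an in-school or out-school youth between 15 and 35 years". No sex restriction appears, and gender is among the "socio-demographic characteristics (such as age, gender, student status, and household size") to be described in section 2.5.
- **Who is excluded.** The exclusions named for all participants concern location, age and willingness: "Not an in or out-of-school youth located in the selected LGAs.Not within the age bracket (15–35 years).Does not have the willingness to participate in the". Those for the education arm concern phone access, internet and social media literacy, and willingness.
- **Status of BMI.** The abstract's list of primary outcomes ends with "dietary diversity, anthropometric, and biomarker indicators". Section 2.4.1.7 stands under Primary outcomes and begins: "Study participants will be assessed on their height (m) and weight (kg) to determine their Body Mass Index (BMI"). It uses BMI-for-age for ages 15–18 and the adult WHO categories for ages 19–35, and states no exception. Table 2 places the measurement at baseline and post-intervention.
- **Analysis.** Section 2.5 states: "Mixed model analyses will be used to assess the intervention’s impact on skin carotenoid levels, anthropometrics, and diet diversity score". Arm, time and their interaction are in the model. The adjustment set is specific: "We will control for participant’s age, gender, household size, youth status (out-of-school vs. in-school status), community, and state".
- **Allocation.** Under section 2.2 the arms are not randomised. Selection for nutrition education depends on criteria such as phone access and familiarity with social media.

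Pregnancy, recent delivery and lactation are mentioned nowhere in the article.

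**The concern.** Many of the women eligible for this study are of childbearing age, and section 3.1 says out-of-school youth are deliberately oversampled. A weight taken during pregnancy, or soon after delivery, does not measure the nutritional status that the BMI categories are meant to describe. The rules as stated classify and model such a weight like any other.

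Three consequences need to be kept apart:

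- **Misclassification.** An affected woman can be placed in a higher BMI category for a reason unrelated to diet. Section 2.5 describes categorical outcomes by frequencies and percentages, so this distorts description. No test of BMI categories is specified.
- **Noise.** A few large shifts inflate the variance of BMI change, even if they are equally common in both arms.
- **Possible bias.** Phone access and digital literacy may vary with age and household circumstances, and so may pregnancy. Balance between the arms therefore cannot be assumed. Adjusting for gender does not separate affected from unaffected women, and the other covariates would remove an imbalance only in part.

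**Working it through.** **The plan's own figure.** Section 2.2.1 gives n = z²p(1−p)/ε² with z = 1.96, p = 0.188 and ε = 0.05. That is 3.8416 × 0.188 × 0.812 / 0.0025 = 234.6, so 235, as stated. Allowing for 10% dropout gives 235/0.9 = 261.1 (262), or 235 × 1.1 = 258.5 (259). Both agree with the stated figure of about 260. This calculation concerns the precision of a proportion and says nothing about BMI, so the consequence has to be sized separately.

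**Inputs**
- From the article: 130 per group less 10% dropout = 117 completers per arm; two-sided 0.05 (the article gives 0.05 without sidedness).
- Assumed, not in the article: half of participants are women; 5–15% of women are affected at exactly one of the two visits, so p = 2.5–7.5% of participants; BMI shift d = 2–4 kg/m²; SD of BMI change otherwise s = 1.0–1.5 kg/m².

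**Noise.** Var(change) = s² + p(1−p)d².

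| p | d | added variance | SD at s = 1.0 | SD at s = 1.5 |
|---|---|---|---|---|
| 0.025 | 2 | 0.0975 | 1.05 (+5%) | 1.53 (+2%) |
| 0.05 | 3 | 0.4275 | 1.19 (+19%) | 1.64 (+9%) |
| 0.075 | 4 | 1.11 | 1.45 (+45%) | 1.83 (+22%) |

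The standard error of the arm contrast rises in the same proportion.

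**Bias.** If all shifts have the same sign, bias = 0.5 × (difference between arms in the share of women affected) × d.
- Lower end: 0.5 × 0.05 × 2 = 0.05 kg/m².
- Upper end: 0.5 × 0.10 × 4 = 0.20 kg/m².
- With no difference between arms, the bias is 0 and the type I error stays at 0.05.

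**Scale.** The difference detectable with 80% power is (1.96 + 0.842) × s × √(2/117), which is 0.37 kg/m² at s = 1.0 and 0.55 at s = 1.5. By normal approximation, with d = 2–4 and s = 1.0–1.5, the two-sided type I error is:
- about 0.057–0.093 if 5% of women are affected in one arm and 10% in the other;
- about 0.079–0.23 if the shares are 2% and 12%.

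**Direction of shifts.** A woman affected at baseline tends to show a fall, and one affected at follow-up a rise. Where both occur, the mean shifts partly cancel and the bias is smaller than shown. The noise does not cancel: with evenly split signs the added variance is pd², slightly more than p(1−p)d².

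**The case against.** The strongest objection is that this is silence in a condensed article. Section 2.2.2 calls its list a summary and introduces the exclusions with an open verb. Section 2.5 gives the socio-demographic items as examples, and Table 2 has one unitemised row for them. The questionnaire is not shown. A reader might infer that pregnancy status is not recorded and that affected values could never be identified. The article does not support that; it shows only that no recording is described. What survives is narrower: the BMI rule in 2.4.1.7 covers participants without exception, and the covariate list in 2.5 is specific. Both treat affected weights as ordinary, whether or not a survey item exists.

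A reader might also infer that pregnancy weight change will be analysed as an intervention effect. That does not follow. The effect is the between-arm difference in change, so balanced pregnancy costs precision and creates no effect. Bias needs an imbalance beyond what the covariates absorb, and none is shown.

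The sizes are assumed, and the bias figures sit at the upper end. The interval between weighings is not stated: the one-year rule in 2.2.2 is a condition on residence or enrolment, and the education component lasts 10 weeks. A short interval would shrink the shift. Even 0.20 kg/m² is below the detectable difference.

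Finally, BMI is one of several primary outcomes, and the hypotheses in 2.1 do not name anthropometry. This limits the weight of the point but does not remove it, because 2.4.1 lists anthropometry as primary and 2.5 models it.

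**Conclusion.** The concern holds in a limited form. The article describes no exclusion, recording or adjustment for pregnancy or recent delivery, while applying its BMI classification and its anthropometric model to all participants. Affected women would be misclassified and BMI change would be noisier, with an SD about 2–45% higher on the assumed inputs. The contrast would also be biased if the frequency or timing of pregnancy differed between arms, by at most about 0.05–0.20 kg/m² for a 5–10 point imbalance among women. It would be biased less if baseline and follow-up pregnancies offset each other or the interval is short.

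The share of women, the share affected, the size of the shift and the SD of change are all assumptions. The weight argument does not reach nutrition knowledge, self-efficacy or skin carotenoids. The change is worth making because it is cheap and because status not collected at the visits would be hard to recover later.

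**What to change.** Keep these women eligible; recruitment need not change.

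1. If the questionnaire does not already do so, add one confidential self-report item at baseline and post-intervention: currently pregnant, or delivered within a stated recent period.
2. State in 2.4.1.7 and 2.5 that BMI values from affected visits are omitted from BMI classification and from the anthropometric mixed model. Keep these women in all other outcomes.
3. Report the number affected by arm and visit, so that any imbalance can be seen.

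**Cost.** One survey item at two existing visits and a sentence in each of two sections. The question is sensitive, and a few BMI values are lost. At 2.5–7.5% of 117 that is about 3–9 participants per arm with one value omitted. Even if each were lost entirely, the standard error would rise by a factor of 1/√(1−p), which is 1.01–1.04. That is a smaller loss of precision than keeping the affected values in any of the cases tabulated above.

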### Theoretical basis

2.3

The Cognitive Theory of Multimedia Learning (CTML), Social Cognitive Theory (SCT), and Empowerment Theory (ET) will inform the intervention. CTML informs the development of effective multimedia messages engaging working memory through two learning channels-verbally and pictorially, enabling readers to construct mental links among visual and textual representations (41). Participants would be required to fuse the new information with the previous knowledge to create a mental representation for the information to be retained (41), activating both verbal and pictorial learning models for the participants will create a piece of integrated information in the working memory through active processing.

Given the focus on social cognitive outcomes such as nutrition knowledge and vegetable and fruit-specific self-efficacy in this study, the SCT will be utilized. This theory posits that human behavior results from the interactions between personal factors, environmental influences, and behavioral patterns. In addition to addressing personal and behavioral outcomes on SCT, this study will also consider relevant environmental factors identified in previous studies as barriers to the use of IVF innovations. These factors include inadequate funding, lack of access to inputs, institutional support, and community influences (42, 43). Also, the study will use ET, which is a social work theory that helps people gain control and autonomy in their lives (44, 45). Our study will include individual-empowered outcomes such as self-efficacy, skill building, access to resources, or resource mobilization skills. Others will include community involvement and institutional participation. Figure 2 summarizes the relationship between CMLT, SCT, and ET principles, highlighting three key aspects: psychological, community, and social empowerment. This framework specifically focuses on the participants in Group 2, who were involved in climate-smart school-based gardening and WhatsApp nutrition education.

**Figure 2 fig2:**
[figure not shown]
Intervention framework for the WhatsApp nutrition education component of the study.

#### Intervention plan

2.3.1

The school-based gardening component of the intervention, as illustrated in Figure 3, will kick off with a 2-day workshop among the targeted participants. This workshop will cover topics such as an introduction to IVF farming and seed production process, showcasing the best soil management practices, and nutrition and food safety education. The participants will also be introduced to digital tools in agriculture, particularly the use of virtual assistants to facilitate sustainable and efficient farming practices, streamlining workflows and revolutionizing how young farmers access expert-level advice virtually, at their convenience. They will also educate participants on agribusiness models for farming and farming-related commercial activities. After the workshop, the youths will be apportioned equal plots for farming on school farmland. Through the collaboration of the school authorities and communities, the out-of-school youths will also have plots to use on the school farmland. The participants will be provided with viable seeds and other farm equipment, such as drips, knapsacks, soil improvement materials etc. to facilitate their farming activities. This will give them the opportunity to utilize the knowledge of IVF farming learned during the workshop. The agricultural science teachers in the selected schools will supervise the new farmers’ work to support community ownership. Furthermore, participants will be provided with technical support to guide them on good soil health management using the climate-smart approach throughout the farming year. Technical support will be provided through both physical and virtual approaches. At the initial stage of transplanting, the technical support will be provided weekly and then fortnightly till the vegetables are well established. Specifically, support will be provided physically to farmers in rural or semi-urban areas who have limited access to internet facilities and electricity, ensuring compliance. In contrast, urban participants will receive support through both physical and virtual means. Leveraging virtual support technology will help save costs and reduce risks associated with city traffic.

**Figure 3 fig3:**
[figure not shown]
Intervention framework for the school gardening component of the study.

Participants selected for the WhatsApp nutrition education will be exposed to the nutrition education curriculum; *Roots and Greens: A Youth Guide to Indigenous Foods and Nutrition (Roots and Greens Curriculum)* for 10 weeks. The curriculum will educate them about the values and uses of indigenous vegetables and fruits. Table 1 describes the content of the *Roots and Greens Curriculum*. The nutrition education intervention involves the use of documents guide, furnished relevant infographics, images, and short video clips. Videos are necessary to make learning interesting and concepts easy to comprehend, which has the propensity to save time reading large texts. The efficacy of video to enhance learning has been widely reported in extant literature (44, 45). This aspect of the intervention will apply interactive tools to create a supportive environment that educates and empowers youth towards sustainable diets, inclusive of IVFs, through quizzes, polls, and group discussions. Table 2 shows the timeline of the study activities according to the intervention stages.

**Table 1 tab1:** *Roots and Greens* curriculum for a 10-week WhatsApp nutrition education.

Week	Topics	Objectives	Activities	Tasks
1.	Introduction to healthy eating	Introduce the concept of healthy eating and familiarize students with indigenous vegetables and fruits (IVFs)	Introduction to healthy eating including an activity on creating a balanced meal plate using provided food options that feature IVFs	Participants will be asked to find a recipe that includes IVFs and share in the group chat
2.	Introduction to IVFs	Familiarize students with indigenous vegetables and fruits.	Identification of commonly known indigenous vegetables and fruits by difference in taste, availability, and perceived nutritional values.	Participants will be asked to cook with an indigenous vegetable at home, document the process with photos and a brief description, and share their experience in the group chat
3.	Nutritional benefits of IVFs	Deepen understanding of the nutritional benefits of IVFs	Discussion of food photos from week 2 task and introduction to the health benefits of IVFs	Participants will be asked to share one indigenous vegetable or fruit they ate this week and mention one health benefit they know about it and share same in group chat
4.	Cultivation and harvesting of IVFs	Teach participants how to grow and harvest IVFs	Introduction to gardening and caring for the plants	Participants will be asked to keep a gardening journal and document the growth and care of their plants
5.	Cultural significance and traditional uses of IVFs	Explore the cultural significance and traditional uses of IVFs	Cultural storytelling and guest speaker session	Participants will be asked to share family traditions or recipes that include IVFs in the group chat
6.	Food safety practices	Understand the importance of food safety and best practices	Introduction to food safety, identifying food safety hazards, and safe handling and preparation of IVFs	Participants will be asked to create a food safety checklist and share same in the group chat
7.	Health benefits and disease prevention	Discuss the health benefits of consuming IVFs nd their role in disease prevention	Health benefits overview and role in disease prevention	Participants will be asked to share personal or family stories where diet changes particularly incorporating IVFs fruits have positively impacted health
8.	Putting it all together: cooking and meal planning	Integrate knowledge to cooking and meal planning with indigenous foods	Cooking techniques, meal planning, and cooking activity	Participants will be asked to implement the meal plan and report back on any challenges
9.	Indigenous foods and sustainability	Understand the role of indigenous foods in sustainable eating practices	Sustainability overview, interactive activity, and group project activity	Participants will be asked to implement a sustainable practice at home and report back any challenges
10.	Review and celebration	Review key concepts and celebrate achievements	Review quiz	Participants will be asked to record (audio) of a reflection of their experience about *Roots and Greens*, include what they have learned and how they have applied it and share it on the group page

**Table 2 tab2:** Study activities and outcome measures according to the stages.

Stage of intervention	Recruitment	Baseline	Intervention period	Post-intervention evaluation
Verbal consent for screening	√			
Eligibility screening	√			
Study invitation	√			
Participants consent		√		
Goal setting for the groups			√	
2-day workshop on gardening activities			√	
Land apportioning for gardening activities			√	
Provision of seeds and farm equipment			√	
Supervision of gardening activities			√	
Technical guide support for the gardening activities			√	
Multimedia messaging for WhatsApp education intervention group			√	
Tracking WhatsApp education participants’ engagement and knowledge retention			√	
Participants’ socio-demographic characteristics		√		√
Participants’ awareness and interest in indigenous vegetables and fruits		√		√
Participants’ household food security		√		√
Participants’ nutrition knowledge and practices		√		√
Participants’ fruits and vegetables specific self-efficacy		√		√
Participants’ food safety self-efficacy and practices		√		√
Participants’ dietary diversity		√		√
Participants’ anthropometric measures and biomarker data collection		√		√

